## 2 STUDY SYNOPSIS

Facility congestion is a significant concern in Zambia. With demand for treatment greater than the available capacity of health infrastructure, the MOH and other stakeholders are concerned about the effect that congestion within facilities may have on patient retention in Antiretroviral therapy care, particularly in urban areas.

We intend to conduct a rapid impact evaluation as part of the DFID funded Demand-Driven Evaluations for Decisions project. This proposal has been designed in response to the question demanded by the Ministry of Health in Zambia ‘How to decongest busy ART clinics in Lusaka.’ We seek to generate reliable impact evidence that meets the Ministry’s needs and is used to catalyze implementation of cost effective action.

This proposal outlines a study with two components. The first being an intensive assessment period during which time, critical process failures are identified that prevent the provision of 3-month ART refills and the design of an intervention that improves clinic efficiency and improves the supply of ART commodities. The second component is a matched, randomised difference in difference study that will determine the effectiveness of the intervention.

We hypothesise that improvements to clinic efficiency and improving the supply of ART stocks will result in a higher proportion of patients receiving 3 month refills, which in turn will reduce the frequency of patients visiting the ART clinic by up to a third and the congestion level of the clinic will improve.

### 3 GENERAL INFORMATION

#### 3.1 *Protocol full title*

Determining the impact of clinic efficiency and supply chain quality improvement interventions on antiretroviral therapy refill length: A matched, randomised difference in difference study

## 4 AIMS

The primary aim is to determine the impact of clinic efficiency and supply chain quality interventions on the proportion of stable patients on 3-month refills at 4 months post intervention.

The secondary aims are as follows:

- a) Estimate the effectiveness of improved clinic efficiency and supply chain quality on other factors associated with antiretroviral therapy (ART) outcomes at 4 months post intervention such as patient wait times and patient satisfaction
- b) Assess the factors that enable the intervention to be successful, including qualitative process measures
  - Patient satisfaction and perceptions of quality of care
  - Patient experiences with transition to multi-month refills
  - Patient and clinician perceptions on reliability of supply chain
  - Clinician perspectives on barriers or challenges to providing multi-month refills
  - Compliance to quality improvement standard operating procedures

### 4.1 *Objectives*

The primary objectives are:

1. Critically assess the failures and challenges related to clinic efficiency and supply chain and their role in preventing the provision of 3-month ART refills.
2. Plan and execute a set of interventions based on the assessment of failures and challenges related to facility congestion.
3. After implementation of the interventions, to determine their impact on the proportion of stable ART patients on 3-month refills.

## 5 BACKGROUND AND RATIONALE

### 5.1 *Introduction*

Demand-Driven Evaluations for Decisions (3DE) is a three-year program funded by DFID. The program supports rigorous impact evaluation in areas of utmost importance to the Ministry of Health (MOH). It seeks to generate reliable impact evidence that meets the Ministry's needs and is used to catalyze implementation of cost effective action. This protocol is a 3DE Evaluation, and as such, this research question was demanded by the MOH.

### 5.2 *ART Clinic Congestion*

In June 2013, the WHO released guidelines that increase the number of people eligible for antiretroviral therapy (ART) from close to 17 million to more than 26 million people in low- and middle-income countries. This decision reflects significant evidence that increasing treatment coverage and access to high-impact prevention interventions will be a crucial next step in turning the tide of the AIDS epidemic. However, despite significant treatment scale-up over the past decade, countries in Sub Saharan Africa are far from achieving the target of universal access for all those in need and will face numerous challenges in scaling up HIV treatment. In particular, the infrastructure, health system and human resources required to properly provide and monitor treatment are extensive, and current systems have limited capacity to support scaled-up ART programs. With the roll-out of strategies to improve access for treatment such as Option B+, existing ART facilities are crowded and burdened, and with the continued scale-up of the provision of ART, they will continue to become increasingly congested.

---

 Eligibility under the 2010 Guidelines was originally estimated at 15 M and has since been revised based on changes in the epidemic and modeling. Global Update on HIV Treatment 2013. WHO Report.

Facility congestion is a concern in Zambia where only 450 accredited health facilities provided treatment to approximately 566,000 patients in 2013. Based on the UNAIDS Gap Report, only about one third of HIV positive patients are accessing treatment, suggesting that there are a total of over one million patients are estimated to be in need of ART in Zambia. Although the MOH is building 650 more ART accredited health facilities to meet the demand, it is essential to identify opportunities for increased efficiencies in order to accommodate these patients. With demand for treatment greater than the capacity within Zambia, the MOH and stakeholders are concerned about the effect that congestion within facilities may have on patient retention in ART care, particularly in urban areas.

Although there is an absence of published literature regarding the implication of congestion on patient retention in ART care, there is evidence to suggest that congestion may affect patient flow and wait times. Moreover, experienced health staff within Zambia have reported that long wait times lead to decreased ART retention, and subsequently, poor treatment outcomes.

### *5.3 ART refill length*

One factor affecting facility congestion is the proportion of stable ART patients receiving 3-month refill prescriptions. With longer prescription refill length, as compared to the frequently dispensed 1- or 2-month prescriptions, stable patients are able to space out their facility visits, and thus, reduce the number of people within the facility at any given time. The Zambian ART Guidelines recommend that stable ART patients be provided with prescriptions for up to 3 months at a time, but few patients in Zambia receive such prescriptions.

To assess refill patterns within Zambian facilities, our team conducted assessments at five ART clinics in Lusaka. The majority of patients received their ART refill for one month or less (51%), 26% of patients received a 2-month refill and 23% received a 3-month refill. The decision on the ideal refill length is often decided by a team (including adherence counsellors and clinicians), however the pharmacist made the final decision based their knowledge of drug stock levels. The In-Charge of facilities reported that unreliable stocks of ARTs were the main barrier to the provision of 3-month refills for stable patients.

### *5.4 Program description and theory of change*

With the aim of improving facility-level congestion and based on the results from the preliminary assessment, interventions are being proposed to address facility specific issues centered on clinic efficiency and supply chain quality. A potential theory of change is listed below:

[figure not shown]

### 5.5 Rationale for Study

The purpose of this work is to outline the impact of the potential intervention for ART clinic efficiency and supply chain quality on facility congestion as measured by the proportion of stable ART patients on 3-month ART prescriptions. We aim to develop and test clinical efficiency and supply chain quality interventions that can be utilized in public, urban facilities throughout Zambia, in order to facilitate the process of scaling up access to ART in Zambia.

## 6 RESEARCH PLAN

### 6.1 Study design

We will conduct a cluster randomised, pair-matched, difference in difference study to assess the impact of the intervention on the proportion of 3-month refill scripts. To assure that the two arms (i.e. the control and the intervention arms) are as comparable as possible, facilities will be matched into pairs based on important factors associated with the primary outcome including the proportion of patients on 3-month refills at baseline, the size of the facility, staff-to-patient ratio (active ART patients) and distance from the Medical Stores Limited (MSL). After pair matching, one facility from each pair will be

randomly assigned to undergo the intervention with a 3-month period of assessment and baseline data collection, followed by a 4-month period of the intervention. To assess facility-level outcomes data will be collected in various formats including patient records, patient exit interviews, provider interviews and other relevant key informant interviews.

#### 6.1.1 Study population

For this work, the study population will be ART facilities within the Lusaka region of Zambia. Patient study population are those who attend one of 16 selected ART facilities within Lusaka, Zambia from August 2014 to March 2015.

#### 6.1.2 Sampling methodology

There are four types of sampling methods based on the method of data collection: facility, patient records, patient exit interviews, and key informant interviews (including health providers and District and MSL staff responsible for ART supply)

- Facilities will be purposefully selected based on the proximity within the Lusaka catchment area and to assure specific key facilities are within the sample for the purposes of policy decisions. Within each facility, one key informant staff member will be interviewed to provide facility-level information.
- Adult (aged 18 or more) patient records will be collected for all eligible patients who receive care at the facility within the time period (provided they meet our eligibility criteria).
- For patient exit interviews, patients will be randomly selected throughout certain days to assure there is a representative sample of the ART facility patients. To this end, every 10th patient to leave the facility will be asked to participate in an exit interview. If this patient does not wish to participate, the immediate next participant will be approached.
- For key informant interviews, clinicians (including doctors, clinical officers, nurses and pharmacists) will be purposefully selected to provide a range of perspectives and experiences.

#### 6.1.3 Study schema

[figure not shown]

## Primary Outcome

The primary outcome is the proportion of stable ART patients receiving 3-month refills, defined as:

The number of stable patients given a 3-month refill in the previous month divided by the total number of stable patients seen in the last month.

Stable patients are defined as:

A patient active in ART care for more than 6 months and on first-line treatment as outlined in the Zambia Consolidated Guidelines (includes the following combinations **(1)** TDF + XTC + EFV, **(2)** TDF + XTC + LPV-r, **(3)** TDF + XTC + ATV-r, **(4)** TDF + XTC + NVP+, **(5)** AZT + 3TC + LPV-r, **(6)** ABC + 3TC + LPV-r, **(7)** ABC + 3TC + EFV).

Secondary outcomes include:

- Patient wait times based on the daily average wait time from entry into the clinic to medication delivery
- Compliance to quality improvement standard operating procedures
- Patient satisfaction and perceptions of quality of care
- Patient experiences with transition to multi-month refills
- Provider perspectives on process of implementing clinical efficiency and supply chain interviews and on barriers or challenges to providing multi-month refills
- Patient and provider perceptions on reliability of supply chain

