## 6.5 Primary and secondary analyses

Firstly, to assess the ability of the matching to produce comparable groups, the characteristics of the matching factors will be compared between the control and intervention group at baseline. Secondly, to assess the presence of other potential confounders, facility-level factors such as the age distribution of the patients or proportion of the population female will be compared between the two groups.

Bivariable comparisons will also compare how these potential confounders are associated with the primary outcome. After examining the success of the matching and the existence of other potential confounders, the remaining analyses will continue with matched analytical methods.

The primary analysis will be a matched comparison of the difference between the intervention and non-intervention facilities in the change of the proportion of eligible patients on 3-month refills overtime (from baseline – endpoint) adjusted for pair-matching and other relevant indicators. The denominator will include all stable patients active in care at the endline. To this end, for bivariable comparisons, we will run McNemar’s matched methods to compare the difference between the proportions between the matched pairs. For further adjustments for potential confounders, conditional multivariable models will be run to examine the difference in the proportion of increased 3-month refills between the intervention and the non-intervention groups.

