## ART Register Data Collection Form

### VERIFICATION AND FACILITY INFORMATION

|                                      |             |                  |                          |
|--------------------------------------|-------------|------------------|--------------------------|
| Data is complete and accurate | Name | Signature | Date (dd/mm/yyyy) |
| 2.1 Enumerator                |             |                  | / / 2014                 |
| 2.2 Supervisor                |             |                  | / / 2014                 |
| 2.3 Name of facility          |             |                  |                          |

ELIGIBILITY: ALL PATIENTS ON 1ST LINE TREATMENT, 18YEARS OLD OR OVER WHO MADE AT LEAST ONE APPOINTMENT DURING THE PREVIOUS 3 MONTHS

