### PATIENT INFORMATION

| 2.4 Patient ID number | 2.5 Sex (M/F) | 2.6 Date of Birth (dd/mm/yyyy) | 2.8 Drug(s) dispensed | 2.9 Dose/ Frequency | 2.10 Quantity | 2.11 Next visit (dd/mm/yyyy) |
|-----------------------|---------------|--------------------------------|-----------------------|---------------------|---------------|------------------------------|
|                       | M F           |                                |                       |                     |               |                              |
|                       | M F           |                                |                       |                     |               |                              |
|                       | M F           |                                |                       |                     |               |                              |
|                       | M F           |                                |                       |                     |               |                              |

*NOTE: This data will be collected electronically where it is available.*

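### The primary outcome has two unreconciled denominators; the one-month version is a visit-weighted share that the intervention itself alters, so the result and the midline stopping decision depend on which is used

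*Combined protocol and SAP*

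**What the plan says.** Four places bear on how the primary outcome is counted.

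- Section 4 (Aims) sets the target as "the proportion of stable patients on 3-month refills at 4 months post intervention". This is a share of patients.
- Primary Outcome (under Section 6.1.3) defines the numerator as "The number of stable patients given a 3-month refill in the previous month". For the denominator, it says that this count is to be "divided by the total number of stable patients seen in the last month". Numerator and denominator both cover a single month of attendance.
- Section 6.5 describes the primary analysis as a matched comparison of "the change of the proportion of eligible patients on 3-month refills overtime" and adds: "The denominator will include all stable patients active in care at the endline". It gives no new numerator and does not say what makes a patient active.
- Annexes 1 and 4, the register and pharmacy forms, take in patients on first-line treatment aged 18 or over "WHO MADE AT LEAST ONE APPOINTMENT DURING THE PREVIOUS 3 MONTHS".

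Three linked facts matter. The Study Synopsis expects visit frequency to fall by as much as a third. Section 6.5.2 stops the study at midline on a 20 percent difference between arms, and Section 6.5.3 places midline after about two months. Endline is at 4 months.

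**The concern.** Two analysts following this plan could report different primary results from the same records. One would divide by patients seen in a month, the other by all active patients.

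The choice matters because the intervention changes how often patients appear. A patient on 3-month refills is seen in one month of three. A 1-month patient is seen every month and a 2-month patient every second month. A ratio over patients seen in one month therefore gives 3-month patients too little weight as a measure of the share of patients. Patients newly moved to 3 months drop out of that denominator until they return. This happens in the intervention arm, so neither randomisation nor differencing removes it.

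The primary estimate is at stake, and so is the midline stopping decision, since Section 6.5.2 does not say which measure it uses.

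**Working it through.** The plan gives no figure for how one definition translates into another, so there is none to reproduce. Section 6.4 plans on changes of 13% and 1% without saying which definition they refer to.

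**Inputs.** Section 5.3 gives a refill mix of 51% (one month or less), 26% (2 months) and 23% (3 months). It does not settle whether these are shares of visits or of patients, so both readings are run. My assumptions: visit dates evenly spread at the start, patients return on time, no change in control.

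**Measures.** The *seen ratio* is 3-month refills given in the month / patients seen in the month. The *hybrid* is the same numerator / all active patients. The *patient share* is patients whose latest refill was 3 months / all active patients.

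**Steady state.**
- Patient reading: patients seen per month = 0.51 + 0.26/2 + 0.23/3 = 0.717, of whom 0.077 get 3 months. A true 23% reads 0.077/0.717 = 10.7% on the seen ratio and 7.7% on the hybrid.
- Visit reading: weights 0.51×1, 0.26×2, 0.23×3 sum to 1.72, so the patient mix is 29.7/30.2/40.1%. A true 40.1% reads 23.0% on the seen ratio and 40.1/3 = 13.4% on the hybrid.
- If every patient were on 3 months, the hybrid would read 1/3 = 33.3%.
- A true +14 points reads +11.5 (visit) or +8.4 (patient) on the seen ratio, and 14/3 = +4.7 on the hybrid.

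**Month by month, refill length persisting within a patient.** Visit reading, conversion at the first visit: the fraction converting is 0.14/0.599 = 0.234.
- Month 1: 0.297 + 0.151 = 0.448 non-3-month patients attend, and 0.448×0.234 = 0.105 convert. Hybrid = 0.134 + 0.105 = 23.8%. Seen ratio = 0.238/0.581 = 41.0%.
- Month 2: the other half of the 2-month patients attend, and 0.151×0.234 = 0.035 convert. The converted 1-month patients (0.297×0.234 = 0.069) are absent, so 0.512 are seen. Hybrid = 16.9%. Seen ratio = 0.169/0.512 = 33.0%.
- Month 4: the month-1 converts return. Hybrid = 23.8%. Seen ratio = 41.0%.

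Under gradual uptake there is a constant chance of conversion at each visit (8.6% visit reading, 5.9% patient reading), chosen to give the same true +14 at month 4. Changes in points:

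| Section 5.3 mix read as | Uptake | True, month 2 | Seen ratio | Hybrid | True, month 4 | Seen ratio | Hybrid |
|---|---|---|---|---|---|---|---|
| visits | instant | 14.0 | 10.0 | 3.5 | 14.0 | 18.0 | 10.5 |
| visits | gradual | 7.5 | 7.6 | 3.6 | 14.0 | 15.0 | 7.0 |
| patients | instant | 14.0 | 5.4 | 2.4 | 14.0 | 16.2 | 11.6 |
| patients | gradual | 7.4 | 5.7 | 3.6 | 14.0 | 11.5 | 7.0 |

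**Refill length set afresh at each visit** (23% rising to 37%, visit reading). The seen ratio is 37% every month, a steady +14. The hybrid reads 21.5, 19.5, 17.7 and 19.5% in months 1 to 4 against 13.4% in control.

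**Stopping rule**, reading 20 percent as percentage points (visit reading).
- Instant conversion of half the other patients, true difference 29.9: month 2 reads 25.3 on the seen ratio and 7.6 on the hybrid.
- Gradual conversion at 30% per visit: month 1 converts 0.448×0.3 = 0.134. Month 2 converts (0.297×0.7 + 0.151)×0.3 = 0.108. The true difference is 24.2. Patients seen = 0.581 − 0.297×0.3 = 0.492. The seen ratio is (0.134 + 0.108)/0.492 = 49.0%, or +26.0. The hybrid is +10.8.

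Both cases stop the study on one ratio and continue it on the other. At the planned size of effect neither ratio reaches 20 at month 2, as the table shows.

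**The case against.** The strongest reply has four parts, and much of it stands.

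- **The seen ratio answers a question the plan also asks.** Section 6.1 describes the outcome as the proportion of 3-month scripts, which a visit-based ratio measures. Section 5.3 has the pharmacist deciding from stock levels, so refill length may not persist; the ratio is then steady by month. This stands. It shows that the estimand is unresolved, not that the two sections agree.
- **Section 6.5 need not miscount.** A reader might infer that both denominators are wrong. Being on 3-month refills can be read as a count of current status over active patients, which has no 33% ceiling. The ceiling applies only if the one-month numerator is carried over. That is, however, the only numerator the plan defines.
- **The swings depend on how uptake happens.** A reader might infer that a real effect could read as zero. In the model, zero occurs only on the hybrid, with instant conversion, at month 3, when no analysis is planned. Gradual uptake damps the swings, and on the visit reading the seen ratio then stays within 3 points of the truth in every month. The intervention was still to be designed and could be revised after two months, so instant conversion is not supported.
- **Two further inferences are not established.** Section 6.5 does not clearly restrict the baseline to patients retained to endline, so selection on retention is not shown. Annex 4 prints "2.6 Date of Birth (dd/mm/yyyy) | 2.8 Drug(s) dispensed" with no dispensing date in view, but column numbers also skip on Annex 1, so this may be numbering or extraction. Annex 1 records the latest appointment, Annex 4 the quantity and next visit, and Section 6.3.1 links the two sources.

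**Conclusion.** The primary outcome is wrong as written: the two sections give different denominators, the forms use a third window, and no text reconciles them. This follows from the documents alone.

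Two consequences follow from visit arithmetic when patients differ lastingly in refill length. The seen ratio understates the level of the share of patients on 3-month refills, and the hybrid is capped near 33% in steady state.

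The effect on the estimate is less certain. For a true +14 at month 4 with persistent refill length, the seen ratio reads about +11 to +18 and the hybrid about +7 to +12, across both uptake patterns and both readings of Section 5.3. With length set afresh at each visit, the seen ratio has no month dependence. The documents do not establish one specific bias at endline. A split midline decision is possible, but in the cases run it arises with true month-2 differences of about 24 to 30 points, above those planned.

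**What to change.** Use one definition in the Primary Outcome text and in Section 6.5, applied identically at baseline, midline and endline.

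- **Denominator:** stable adults with at least one dispensing in the preceding 3 months, close to the appointment window already printed on Annexes 1 and 4, plus a short stated grace period for late returners.
- **Numerator:** those among them whose most recent dispensing was a 3-month supply.
- **Section 6.5:** replace the reference to being active at endline with active at that time point, and define active as above.
- **Sections 6.4 and 6.5.2:** state that the planned changes and the midline threshold refer to this measure.
- **Data:** confirm that the dispensing date is captured on Annex 4 or can be derived from the linked register and pharmacy records.
- **Secondary measure:** keep the share of last-month visits ending in a 3-month refill as a measure of prescribing.

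The cost is a few sentences and, at most, one date column. With instant conversion of 20% of the other patients, this measure differs between arms by 9.0 points in month 1 and 12.0 in months 2 to 4. The drawback is that the window includes some earlier dispensings, so the measure lags slightly, most of all at midline.
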